#### Interim analysis population

The interim analysis population will include all patients who have been recruited at the time 300 patients have completed 90 days follow-up, including patients with partial data (e.g. anyone recruited after the 300th patient who has not yet completed their follow-up, and anyone recruited before the 300th patient who left the trial before completing follow up). If there is greater than 15% missing data for DAH90 (excluding missingness because of death, which is informative) and the interim analysis is delayed because of that, the interim analysis population may include more than 300 patients. The trial will recruit from the UK, Australia and New Zealand. It is expected that the majority of the patients recruited by the end of the trial will be from UK centres. To ensure that the results of the interim SSR reflect the expected proportions of UK, Australian and New Zealand recruits, we will seek to ensure that between 50 and 75% of the patients included in the interim analysis are recruited from the UK, with the remainder from Australia and New Zealand. This will ensure that even if differences exist between the countries, the effect will not disproportionately bias the interim SSR and therefore will not affect the power at the end of the trial. This requirement may impact on the timing of the interim analysis and may require that more than 300 patients have been randomised and followed up to 90 days to achieve the proportions stated.

#### Intention-to-treat population

The ITT population is the population that will be used for the majority of the analyses, including the analysis of the primary endpoint and the interim sample size re-estimation. The ITT population includes all subjects who were randomised, regardless of whether they received the treatment randomly allocated to them or completed follow-up. The data will be analysed assuming that the patient received the treatment they were randomly allocated to. If a patient dies after being randomised but before extubation occurs, they will be included in the ITT analysis population with a days at home score of zero.

#### Other populations

A per-protocol and two time-on-treatment (ToT) populations are also defined for use in sensitivity analyses. A full population is also defined. These are detailed in the additional document.

### Protocol deviations and adherence

There are two analysis populations relating to protocol non-adherence. The ITT analysis population includes all subjects who were randomised, regardless of whether they received the treatment randomly allocated to them or completed follow-up. The data will be analysed assuming that the patient received the treatment they were randomly allocated. The per-protocol population includes all subjects who adhered to the trial protocol by receiving the treatment randomly allocated for a minimum of 16 h no matter whether they complete all of their follow-ups. Any subjects who did not receive the treatment randomly allocated to them will be excluded from the per-protocol population.

Descriptive statistics of compliance variables will be reported at the final analysis, split by treatment arm. These will include:Summary of treatment complianceReasons for non-complianceSummary of compliance for the ToT populations

### Baseline characteristics

Baseline data will be collected following consent. This will include demographic data (age, sex, residential status, etc.), past medical history, quality of life (EQ-5D-5L), activity of daily living (BARTHEL), health service and resource use questions, the EuroSCORE II and the ARISCAT score. Descriptive statistics summarised by the treatment arm will be reported.

### Interim analysis

The interim analysis will be performed after a minimum of 300 patients have been randomised and followed up for 90 days. If there is greater than 15% missing data for DAH90 (excluding missingness because of death, which is informative missingness) then the interim analysis may be delayed. If at the time 300 patients have been randomised and followed up, the rate of UK participation is outside the target range, the interim analysis may be delayed as per the definition of the interim analysis population.

Three main areas will be examined at the interim analysis:SafetyRecruitment, compliance and data completenessSSR

The safety analyses at the interim analysis will be identical to the safety analyses at the final analysis, described below. Information on recruitment, treatment compliance, and data completeness will be reported at both the interim and final analysis. A summary of patient recruitment data will be presented by the centre, as well as by the treatment group and time or trial stage where appropriate. Compliance and data completeness will be summarised by the treatment group.

#### Sample size re-estimation

Due to uncertainty in the parameters used in the original sample size calculation and the sensitivity of the initial sample size calculation to changes in the nuisance parameters, NOTACS has been designed as an adaptive trial with an interim SSR planned after a minimum of 300 patients complete 90 days follow-up.

This sample size adaptation may prevent an underpowered trial if moderate deviations from the assumptions made for the initial sample size calculation are observed.

At the interim SSR, the accumulated data will be used to re-estimate a number of “nuisance” parameters including:SD of DAH90 in the SOT armSD of DAH90 in the HFNT armTreatment switch rate from SOT to HFNTTreatment switch rate from HFNT to SOTOverall drop-out rateOverall death rate

Treatment efficacy will not be assessed at the interim analysis.

An independent statistician will re-estimate the nuisance parameters using unblinded data (in order to allow the trial statisticians to remain blinded, and to preserve the type 1 error rate at 5%). The original sample size calculation will be repeated with the updated estimates to provide an updated sample size estimate which will be reported to the DMEC. The DMEC have the responsibility of agreeing the updated sample size following the rules in Table 1. Any recommendation outside of those listed in Table 1 should be clearly justified.

**Table 1 Tab1:** Recommended sample size from interim SSR and course of action

Recommended sample size from interim SSR	Course of action
≤850	Continue recruitment to 850 patients
851–1152	Continue recruitment to the new recommended sample size
>1152	Continue recruitment to 1152 patients

No adjustments will be made to the significance level due to the interim analysis.

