### Sample size calculation

Results from the pilot study [7] and information provided by collaborative hospitals were used to derive the required sample size for the NOTACS study. The sample size calculation relied on several nuisance parameters (standard deviation of DAH90 in the SOT arm; standard deviation of DAH90 in the HFNT arm; treatment switch rate from SOT to HFNT; treatment switch rate from HFNT to SOT; overall drop-out rate; overall death rate) that were provided from the single centre pilot study or collaborative hospitals and may differ between sites in the multicentre design. The sample size calculation was performed by simulation due to the non-standard distribution of the primary end-point. Due to uncertainty in the nuisance parameters used and the sensitivity of the sample size calculation to changes in the nuisance parameters, the NOTACS study includes an interim SSR, a type of adaptive design. This will provide protection against important deviations from the initial assumptions in the original sample size calculation and ensure that the study is not underpowered.

DAH90 typically has a left-skewed bi-modal distribution with a small spike at 0 due to in-hospital deaths. The required sample size was obtained by simulations (100,000 replicates) by first generating length of stay (LOS) using a lognormal distribution. Based on the information provided by collaborating hospitals, the parameters of the lognormal distributions in both arms were derived through a pooled weighted average. The variability was calibrated to SD =12.85 in the control arm and SD=3.20 in the treatment arm. The median LOS in the control arm was set to 8 days. We assumed a 3% death rate (based on pilot data [7] and registry data [8]), and following the approach of Myles [9] we treated any death within the 90-day follow-up period as scoring 90 for LOS regardless of when the death occurred. LOS was truncated at 90 days (the maximum for our follow-up period). Finally, DAH90 was computed as 90 minus LOS. The resulting data are bimodal with a spike at 0, as seen with observed data of this type.

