### Analysis for the primary endpoint

The analysis of the primary and secondary endpoints will take place at the end of the trial following database lock.

The primary outcome is DAH90. Following the approach of Myles et al., for the primary analysis, DAH90 will be treated as 0 for any patient that dies in the period between randomisation and the 90-day follow-up [9]. This definition is deemed appropriate on the basis that the death rate in the trial population is expected to be low (around 3%), most deaths are expected to occur within the initial hospital admission, the death rate is expected to be comparable between the two treatment arms, and it is not expected that the treatment will impact on the death rate. The primary analysis will be on the basis of intention to treat (ITT).

Due to the skewed nature of DAH scores, a Mann-Whitney-Wilcoxon test will be used for the primary efficacy analysis. Contrasts between treatment groups for DAH90 will be used to evaluate the difference in the median DAH90 at a 5% significant level. 95% confidence intervals giving a range of plausible effects will be reported. The non-parametric confidence interval will be calculated using either the Hodges-Lehmann method if an exact p-value is available, or a normal approximation otherwise.

The statistical analysis will be reported according to CONSORT extension guidelines for reporting of adaptive trials [10]. A review statistician will independently reproduce the final primary efficacy analysis.

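### The re-estimation names the wrong SD: 12.85 and 3.20 are spreads of length of stay before deaths and switching, and entering SDs of DAH90 in their place drives the sample size to the 1152 cap under the planning assumptions

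*SAP article*

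**What the plan says.** All references are to the SAP article.

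- **Sample size calculation, how the data are generated.** The simulation starts "by first generating length of stay (LOS) using a lognormal distribution". Then: "The variability was calibrated to SD =12.85 in the control arm and SD=3.20 in the treatment arm". Also: "The median LOS in the control arm was set to 8 days".
- **Same section, deaths.** "We assumed a 3% death rate", and "we treated any death within the 90-day follow-up period as scoring 90 for LOS regardless of when the death occurred". LOS is cut off at 90, and the last step converts it to DAH90 as 90 minus LOS. The allowances for 12% and 25% switching and 5% loss come after that and take the total from 310 to 850.
- **Same section, what the inputs are called.** "The sample size calculation relied on several nuisance parameters (standard deviation of DAH90 in the SOT arm; standard deviation of DAH90 in the HFNT arm", followed by the two switch rates, drop-out and the death rate.
- **Sample size re-estimation.** The list of quantities to re-estimate again has the SD of DAH90 in each arm and, as a separate item, the overall death rate. Then: "The original sample size calculation will be repeated with the updated estimates to provide an updated sample size estimate which will be reported to the" monitoring committee. Table 1 keeps 850 for any smaller result and caps any larger one at 1,152.
- **Intention-to-treat population.** This population is named for the re-estimation as well as for the primary endpoint.
- **Analysis for the primary endpoint.** "DAH90 will be treated as 0 for any patient that dies in the period between randomisation and the 90-day follow-up".

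**The concern.** The calculation takes a spread of LOS and adds deaths and switching to it in later steps. The re-estimation list names a different quantity, the SD of the finished outcome, which already contains deaths scored 0 and, by randomised arm, the switchers. Under one label, the article moves from an input of the simulation to an output of it.

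This rule alone sets the final sample size. If an output SD is entered where an input SD belongs, the recommendation is far too large even when nothing has departed from plan. Up to 1152 − 850 = 302 further patients (36%) would then be randomised without need, and the DMEC would be told that a sound trial is badly underpowered. The primary test itself is unaffected.

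**Working it through.** **Inputs.** From the article: control median LOS 8; SDs 12.85 and 3.20; 3% deaths at LOS 90; LOS cut off at 90; 12% and 25% switching; 5% loss; 1:1 allocation; 90% power; 5% level; cap 1,152. Assumed: a two-sided test, and an HFNT median LOS of 8 − 2 = 6.

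**Method.** For a lognormal with median m and SD s, put x = [1 + √(1 + 4(s/m)²)]/2; the log-SD is √(ln x). This gives 0.883 for SOT and 0.456 for HFNT. Switching is a mixture of the two arms' distributions. With θ = P(SOT stay longer) + ½P(tie), power is Φ[(|θ − ½| − 1.96·SE₀)/SE₁], where SE₀ is the tie-corrected null standard error and SE₁ the standard error under the alternative. The total is divided by 0.95 for loss.

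**Step 1: reproduce the plan.** Without switching or loss the total is 306 (stated 310; power at 310 is 90.4%). With both it is 810 if the SDs hold before the cut at 90, or 871 if they hold after it. The stated 850 lies between; power at 850 is 91.3% or 89.3%. So 12.85 and 3.20 act as LOS SDs before deaths and switching.

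**Step 2: they cannot be SDs of DAH90.** If 3% score 0 and all others score exactly 82 or 84, the SD is already √(0.03 × 0.97) × 82 = 14.0 or × 84 = 14.3. Under the planning model, with p = 0.03, variance = (1 − p)s² + p(1 − p)(90 − mean LOS)²:

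- HFNT: 0.97 × 3.20² + 0.0291 × (90 − 6.66)² = 9.9 + 202.1, SD 14.6.
- SOT (SD 11.91 and mean 11.72 after the cut at 90): 0.97 × 11.91² + 0.0291 × (90 − 11.72)² = 137.6 + 178.3, SD 17.8.

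By randomised arm, with switchers, the SDs are 17.5 and 15.6.

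**Step 3: repeat the calculation with every planning assumption true** (SDs taken before the cut at 90).

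| SDs entered as LOS SDs (SOT / HFNT) | Deaths added in the simulation | Total N | Power shown at 850 |
|---|---|---|---|
| 12.85 / 3.20 (as planned) | 3% | 810 | 91% |
| 17.8 / 14.6 (DAH90, no switchers) | 3% | 1,696 | 63% |
| 17.5 / 15.6 (DAH90, randomised arm) | 3% | 1,730 | 62% |
| 17.8 / 14.6 | none | 1,502 | 68% |
| 17.5 / 15.6 | none | 1,532 | 67% |
| 11.4 / 6.9 (survivors, randomised arm) | 3% | 1,018 | 84% |

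If the SDs are taken to hold after the cut, the second and third rows become 2,155 and 2,239.

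**Step 4: split the excess.** Without switchers in the SDs, it is 1696 − 810 = 886. Of this, 1502 − 810 = 692 (78%) arises with no second death spike; adding deaths again gives 1696 − 1502 = 194. The main cause is the HFNT SD going from 3.20 to 14.6.

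**Step 5: sampling variation.** In 2,000 simulated interims of 150 per arm with all assumptions true and SDs by randomised arm, the median recommendation was about 1,720. It exceeded 1,152 in 97.4% (all rates estimated) to 99.4% (rates held at plan).

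**Step 6: other death rates.** With no switchers in the SDs, true death rates of 0.5%, 1%, 2% and 4% give about 976, 1,170, 1,460 and 1,910.

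**The case against.** The strongest reply is that the label is merely loose. The article uses the same name for the inputs of the planning calculation, where it plainly meant LOS spread, so a like-for-like repeat would re-estimate LOS spread again. The rule scoring deaths as 0 is stated for the primary analysis, and nowhere does the article say outright that the interim SD includes deaths. The article condenses a fuller SAP that may define the input properly. The DMEC may also depart from Table 1 with justification.

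Part of this stands. The article does not show what the code does, and a reader who infers that the trial is bound to go to 1,152 goes further than the text allows. But the article does state the quantity, the population, how the outcome scores a death and the rule, and following them gives the wrong number. A name that is safe only if it is not taken literally should be corrected.

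Three further inferences are tempting and do not hold:

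- **That counting deaths twice is the cause.** It is the smaller part; the total is about 1,500 without it.
- **That the rule returns the cap whatever happens.** In expectation it does so from a death rate of about 1% upwards; at 0.5% the total is about 976.
- **That leaving deaths out of the SD is a sufficient cure.** ITT data by randomised arm also contain the switchers, and survivor-only SDs still give about 1,018. Only survivor SDs free of switchers return 767 to 871.

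**Conclusion.** The point holds as an error in the stated input. The SDs 12.85 and 3.20 are spreads of LOS before deaths and switching, and the article labels them SDs of DAH90 both in the planning section and in the re-estimation rule. Read as written, with the ITT population and deaths scored 0, the rule recommends about 1,700 (1,696 to 1,730) when the planning assumptions are exactly true, against 810 to 871 from a consistent calculation. Table 1 would turn that into 1,152, and power at 850 would be shown as about 63% when it is about 90%.

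This rests on a two-sided 5% test, an HFNT median LOS of 6 days, DAH90 being 90 minus LOS with no other component, and the full SAP not defining the SD input otherwise. The first two assumptions are supported by how closely 310 and 850 are reproduced. The error can only enlarge the trial, by at most 302 patients, and does not touch the primary analysis. It should be settled before the interim because this rule alone fixes the sample size.

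**What to change.** 1. In Sample size calculation and in Sample size re-estimation, replace SD of DAH90 by the input actually used: in each arm, the spread of LOS (90 − DAH90) before deaths and before switching.
2. Obtain it by calibration. Choose the two lognormal LOS distributions so that the full simulation, after the estimated switching, deaths and cut at 90, reproduces the SDs observed by randomised arm. Keep the death and switch rates as separate inputs, each applied once.
3. Before the interim, confirm that the code returns about 850 on data simulated from all planning assumptions, including 12% and 25% switching. As a check of the principle, feeding in the expected SDs of 17.5 and 15.6 and solving in this way recovers 12.85 and 3.20, and hence 810.
4. State what is done if no pair of LOS SDs reproduces both observed values exactly, for example taking the closest fit. With about 150 patients per arm this can happen by chance, because the all-patient SDs depend heavily on a few deaths. The check in item 3 should therefore use a large simulated data set or an average over many.

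The cost is a wording change and a small change to the re-estimation code. It needs no new data and no further patients, and the primary analysis stays as it is.

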### Analysis for the primary endpoint

The analysis of the primary and secondary endpoints will take place at the end of the trial following database lock.

The primary outcome is DAH90. Following the approach of Myles et al., for the primary analysis, DAH90 will be treated as 0 for any patient that dies in the period between randomisation and the 90-day follow-up [9]. This definition is deemed appropriate on the basis that the death rate in the trial population is expected to be low (around 3%), most deaths are expected to occur within the initial hospital admission, the death rate is expected to be comparable between the two treatment arms, and it is not expected that the treatment will impact on the death rate. The primary analysis will be on the basis of intention to treat (ITT).

Due to the skewed nature of DAH scores, a Mann-Whitney-Wilcoxon test will be used for the primary efficacy analysis. Contrasts between treatment groups for DAH90 will be used to evaluate the difference in the median DAH90 at a 5% significant level. 95% confidence intervals giving a range of plausible effects will be reported. The non-parametric confidence interval will be calculated using either the Hodges-Lehmann method if an exact p-value is available, or a normal approximation otherwise.

The statistical analysis will be reported according to CONSORT extension guidelines for reporting of adaptive trials [10]. A review statistician will independently reproduce the final primary efficacy analysis.

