#### Secondary outcomes

A series of Mann-Whitney-Wilcoxon tests will be used to assess whether a treatment effect exists for: DAH30; length of ICU stay during index admission; ROX index at 2, 6, 12, 24 and 48 h post-extubation; individual countries; and individual centres (UK only). Difference in medians with corresponding 95% confidence intervals will be reported for each comparison. The non-parametric confidence interval will be calculated using either the Hodges-Lehmann method if an exact p-value is available, or normal approximation otherwise.

Chi-squared tests (or Fisher’s exact test where appropriate) will be used to assess the association between the treatment group with extubation timing (≤ or >24 h after admission to ICU) and return to theatre (≤ or > 24 h of admission to ICU).

To allow for the estimation of effect sizes and adjustment for potential clinically important covariates, quantile regression models will be fitted for DAH90 and DAH30 as outlined in Table 2. Quantile regression was chosen due to the heavily skewed nature of the DAH endpoints and due to the expectation of two spikes close to day 0 and day 90/30.

**Table 2 Tab2:** Quantile regression models

Outcome variable	Explanatory variable(s)	Levels
DAH90	Treatment group	SOT [reference group], HFNT
DAH30	Treatment group	SOT [reference group], HFNT
DAH90	Treatment group ARISCAT risk category EUROSCORE II Gender COPD Asthma Obesity Current smoker Lower respiratory tract infection in last 4 weeks Age First time or re-do surgery Country	SOT [reference group], HFNT Low [reference group], intermediate, high - Female [reference group], Male No [reference group], Yes No [reference group], Yes No [reference group], Yes No [reference group], Yes No [reference group], Yes - First time [reference group], Re-do UK [reference group], Australia, New Zealand

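### The rank-based 95% interval is described as an interval for the difference in median DAH90, but it targets the Hodges-Lehmann shift, and under the plan's own model the two differ

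*SAP article*

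**What the plan says.** The section on the primary endpoint says that "a Mann-Whitney-Wilcoxon test will be used for the primary efficacy analysis". It continues: "Contrasts between treatment groups for DAH90 will be used to evaluate the difference in the median DAH90 at a 5% significant level". The 95% interval is to be "calculated using either the Hodges-Lehmann method if an exact p-value is available, or a normal approximation otherwise". No point estimate is named there, and no pure-shift assumption is stated.

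The secondary outcomes section uses the same test and interval rule for DAH30, ICU stay, the ROX index, and comparisons by country and by UK centre. It adds: "Difference in medians with corresponding 95% confidence intervals will be reported for each comparison".

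The sample size section fixes the planning model. It starts by "generating length of stay (LOS) using a lognormal distribution", with a control median of 8 days. On spread it says: "The variability was calibrated to SD =12.85 in the control arm and SD=3.20 in the treatment arm". It then adds 3% deaths scored as zero days at home, 12% switching from SOT to HFNT, 25% switching the other way, and 5% loss. The target effect is 2 days in the median. Table 2 lists an unadjusted quantile regression of DAH90 on treatment, among the exploratory secondary analyses.

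**The concern.** Inverting the Mann-Whitney-Wilcoxon test gives an interval for the median of all differences between a patient in one arm and a patient in the other, which is the Hodges-Lehmann shift. If one arm's distribution is the other's moved by a constant, that is also the difference in medians. Otherwise the two can differ, and the interval need not cover the difference in medians at its nominal rate.

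The plan assumes distributions that differ in shape, and the re-estimation step updates the two SDs separately, so unequal spread is a design premise. The effect of interest is expressed as 2 days in the median. A reader given a rank-based interval labelled as an interval for the difference in medians would set it against that target on the wrong scale.

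**Working it through.** **Inputs (sample size section).** Lognormal stay; control median 8, SD 12.85; treatment SD 3.20; cap at 90; 3% deaths with DAH90 = 0; switching 12% and 25%; 5% loss; total N 310 without switching and 850 with it. Assumed here: treatment median 6 (8 less the 2-day effect), SDs that apply before deaths are added, switchers who take the other arm's full distribution, and a two-sided 5% test.

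**Log-scale SDs.** With median m and log-SD σ, SD² = m²·u(u − 1), where u = exp(σ²).
- Control: u(u − 1) = (12.85/8)² = 2.580, so u = 2.182 and σ = 0.883.
- Treatment: u(u − 1) = (3.20/6)² = 0.284, so u = 1.231 and σ = 0.456.

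**The plan's own figure.** The tie-corrected test, 20,000 replicates:
- 155 per arm, no switching: power 90.3% (stated 90%).
- 850 × 0.95 / 2 ≈ 404 per arm, planned switching: power 91.4% (stated 90%).

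The model is therefore a fair reading of the plan.

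**True difference in medians with switching.** With 3% deaths at the far end, the median stay is the point where the survivors' distribution function reaches 0.5/0.97 = 0.5155. Write F0 and F1 for the SOT and HFNT lognormals.
- SOT arm: 0.88·F0 + 0.12·F1 = 0.88 × 0.488 + 0.12 × 0.717 = 0.5155 at 7.79 days.
- HFNT arm: 0.25·F0 + 0.75·F1 = 0.25 × 0.399 + 0.75 × 0.554 = 0.5155 at 6.38 days.
- Difference: 7.79 − 6.38 = 1.41 days (1.40 by simulation).

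**Hodges-Lehmann target.** The median of simulated pairwise differences is 1.12 days, a gap of 0.28 day, or 0.28/1.40 = 20%. Without switching the values are 2.17 and 1.85.

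**Coverage of the difference in medians by the inverted rank test, continuous days.** The value d is covered when the test of (HFNT − d) against SOT does not reject.

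| Setting | Coverage |
|---|---|
| 404 per arm, planned switching | 86.8% (12.8% of intervals wholly below the true value) |
| 425 per arm, planned switching | 86.2% |
| 404 per arm, no switching | 86.9% |
| 155 per arm, no switching | 90.7% |
| 547 per arm (1152 less 5%), switching | about 84% |
| 404 per arm, switching, no deaths | 91.7% |

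**Controls.** A pure 2-day shift with equal spread and 3% deaths gives 94.7%. The interval covers its own target, the Hodges-Lehmann shift, 94.2% of the time with switching. The shortfall therefore comes mainly from the label and not from the interval.

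**Whole days.** Order-statistic interval, end points included, 404 per arm, planned switching:
- Stay rounded to the nearest day: medians 8 and 6, difference 2; coverage 81% to 84% across runs.
- Stay rounded up: medians 8 and 7, difference 1; coverage 99.5%.

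Without switching, whole-day coverage was 99.5% to 100%. The treatment of ties matters too. With nearest-day rounding and switching, testing the value 2 directly with the tie-corrected test left it unrejected in only 35% of trials, because 2 is then often the end point itself.

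**Size of the test.** With both stay medians at 8, unequal spreads and the planned switching, the test rejects in 5.1% to 5.8% of trials.

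**The case against.** Several points on the other side are sound.

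- **The 86% is one scenario.** A reader might infer that the interval the trial reports will cover 86% of the time. It will not in general: the figure holds for continuous days at about 404 per arm. Whole-day coverage depends on a counting rule this article leaves to its additional document.
- **The four-fold SD gap is not the whole cause.** With equal log-SDs (treatment SD about 12.85 × 6/8 = 9.6), continuous coverage was still 83% to 89%. Any departure from a pure shift suffices, and a multiplicative effect on a skewed stay is one.
- **The interval rule does not misfire.** A reader might argue that the Hodges-Lehmann branch can never apply with 850 patients and tied values. The article states a fallback, and its use at that size is the rule working as written. Comparisons in small centres or on the ROX index might use the exact branch. What stays open is whether the fallback inverts the rank test, which the 86% assumes.
- **The primary test is not undermined.** One might infer a type I error problem. With planned switching the excess is slight. Rates up to 6.8% arose only without switching, which the plan does not expect. With identical distributions the test keeps its level.
- **A median-difference analysis is already specified.** Table 2 contains it, and the primary section names no point estimate, so an explicit pairing of a difference in medians with this interval appears only for secondary comparisons. But the Table 2 model is exploratory, and the primary section still says that the rank contrast evaluates the difference in the median.

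The gap is about a quarter of a day, and the misses fall mostly on the side that understates benefit. That limits the harm but does not make the label correct.

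**Conclusion.** The mismatch is real and is one of labelling. Under the plan's model on continuous days, with about 404 evaluable patients per arm and planned switching, the stated quantity is about 1.40 days and the interval's target about 1.12. Coverage of the stated quantity is about 86% instead of 95%. This rests on a treatment median of 6 days, full adoption of the other arm's distribution by switchers, and a fallback that inverts the rank test. In whole days coverage ranges from about 81% to 100% for the closed order-statistic interval. The documents do not support a claim of a fixed 86%, of a faulty interval rule, or of a materially inflated type I error. The correction should be made, but neither the design nor the choice of primary test needs to change.

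**What to change.** In the primary endpoint and secondary outcomes sections:

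1. Describe the rank-based estimate and interval as the Hodges-Lehmann shift, obtained by inverting the rank test at any sample size. State how ties and end points are handled.
2. Delete the difference in medians as the description of that estimate and interval.
3. Wherever a difference in medians is reported, including any comparison with the 2-day target, take it and a bootstrap interval from the unadjusted quantile regressions in Table 2 (DAH90 and DAH30). For outcomes and comparisons not in Table 2, bootstrap the sample medians.

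Reporting the probability that a patient on HFNT has a higher DAH90 than one on SOT, plus half the probability of a tie, is optional.

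The cost is SAP wording and a few lines of code. Sample size, primary test and interim re-estimation are unchanged.
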